#### Eligibility Criteria

Patients who will undergo a laparoscopic or open colectomy or hysterectomy and are aged between 18 and 75 years will be contacted. Exclusion criteria are surgery without a curative intention, deep infiltrating endometriosis, concomitant surgical procedures, not able to use the internet, unable to understand Dutch questionnaires, malignancy (in case of the hysterectomy), and receiving neoadjuvant treatment.

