#### Sample Size Calculation

To detect a hazard ratio of 1.4 for RNA (corresponding to a decrease in median time to RNA from 10 weeks to 7.14 weeks as a result of the intervention) with 80% power while testing using a 2-sided log-rank test at a significance level of 5%, a total of 318 events need to be observed. The total sample size is set at 354 (177 per arm) to account for an anticipated proportion of 2.5% of patients not returning to daily activities within the 12 month follow-up period and a dropout rate of 10%.

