#### Recruitment, Inclusion, Allocation, and Blinding of Patients

Patients will be recruited for study participation when they are on the waiting list in one of the participating hospitals and will receive a study information letter on behalf of their doctor. Contact will be made by phone to check their willingness to participate and to access eligibility. Eligible patients willing to participate will be included. After the patient completes the baseline questionnaire T(0) within 2 week before surgery and has signed informed consent, randomization will be executed by an (independent) research assistant. A computer-generated randomization in a 1:1 ratio will be performed on individual level stratified regarding hospital, sex, and surgical procedure using permuted blocks of size 2. Patients will be blinded to the intervention, as they do not know which program is developed as a nonintervention or intervention care program. The researchers involved in the analyses will be blinded to the allocation throughout the analyses. Health care professionals cannot be blinded to the intervention because it is highly likely that they will be notified of the allocation either by the patient or the patients’ medical file.

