#### Data Analyses Plan

All analyses will be performed in IBM SPSS. Baseline characteristics will be summarized using descriptive statistics and compared between the intervention and control group using *t* tests by normal distributions of variables and Mann-Whitney *U* tests, chi-square tests, or Fisher exact tests by non-normal distributions of variables. Our primary outcome, time until full RNA, will be analyzed by both crude and adjusted survival analyses where hospital, surgical procedure, and sex will be taken into account as covariates in the adjusted analyses due to stratification. To describe the distribution of the duration until RNA in both groups, the Kaplan Meier method will be used. The Cox proportional hazard model will be applied to calculate hazard ratios. Adjustments will be made if there are clinically relevant differences between the intervention and the control group in the baseline characteristics or if other potential confounding factors are observed. For the longitudinal secondary outcomes, mixed models and multilevel logistic regression models will be performed. For the cross-sectional secondary outcomes, *t* tests, Mann-Whitney *U* tests, chi-square tests, or Fisher exact tests will be used to compare differences. Intention-to-treat analyses will be compared with per-protocol analyses to identify whether there are differences if patients used the intervention as intended. Subgroup analyses will be performed regarding the surgical procedure (colectomy and hysterectomy) and indication (benign or malignant disease). A post hoc analysis will be carried out on patients without major complications.

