### Comparison With Other Studies

The IM protocol has proven to be suitable to systematically and scientifically develop an eHealth intervention for various health issues [69,70]. In addition, a few studies have also used the IM protocol to further develop, adapt, or adjust an existing intervention [71,72]. In these studies, the IM protocol was considered suitable and enabled researchers to reconsider points of view and to integrate new information into existing tools. These studies used the IM protocol in the same manner as we did in this study. They decided to further build on the methodological choices made in the previously developed intervention by adjusting and improving the existing intervention for a new study population [71,72]. Methodological choices made in steps 2 and 3 of the IM process of developing the original “ikherstel” intervention, as described in the IM article of Vonk Noordegraaf et al, are considered effective and, therefore, used again in this IM procedure [19].

Comparison with other studies focusing on the development of eHealth recovery interventions is limited due to a low number of studies [18,23]. When comparing this developed intervention to the eHealth interventions included in the systematic review conducted by our planning group in step 1, it can be concluded that our intervention consists of multiple components on a diversity of functions that makes this a comprehensive intervention. In addition, most RCTs regarding enhancing the postoperative course are performed in cardiac surgery, whereas there is a lack of RCTs evaluating postoperative recovery after general surgical and gynecological procedures [73-80]. The studies of Vonk et al and Bouwsma et al are most comparable [18,23]. However, our study will be the only RCT that will be performed in patients undergoing major abdominal surgery focusing on RNA, which also includes procedures performed due to a malignant indication [81]. By determining the time until RNA as primary outcome, all patients aged between 18 and 75 years can participate in this study allowing more people to be reached.

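### Run over all patients, the benign/malignant subgroup contrast mixes indication with procedure and sex, because malignant hysterectomies are excluded; base it on colectomies only

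*Protocol article*

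**What the plan says.** In the protocol article, under Step 6 (Evaluation):

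- **Eligibility Criteria.** Both procedures are admitted: "Patients who will undergo a laparoscopic or open colectomy or hysterectomy and are aged between 18 and 75 years will be contacted". One exclusion applies to a single procedure: "malignancy (in case of the hysterectomy". No indication is required for colectomy, so benign colectomies are eligible.
- **Data Analyses Plan.** Procedure and indication are named side by side as subgroup factors: "Subgroup analyses will be performed regarding the surgical procedure (colectomy and hysterectomy) and indication (benign or malignant disease". The sentence does not say that the indication analysis is confined to one procedure. For the adjusted primary analysis, "hospital, surgical procedure, and sex will be taken into account as covariates in the adjusted analyses due to stratification".
- **Recruitment, Inclusion, Allocation, and Blinding of Patients.** Randomization is "stratified regarding hospital, sex, and surgical procedure using permuted blocks of size 2". Indication is not a stratification factor.
- **Comparison With Other Studies** (Discussion). The inclusion of cancer surgery is presented as a distinguishing feature of the trial, "which also includes procedures performed due to a malignant indication".

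**The concern.** The subgroup sentence treats procedure and indication as two separate questions. The eligibility rule ties them together, because one of the four combinations cannot occur. Over all patients, the malignant group is entirely colectomy, while the benign group contains every hysterectomy and whatever benign colectomies are recruited. Hysterectomy patients are women, so sex is mixed in as well.

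Suppose the intervention works better after hysterectomy than after colectomy, for reasons unrelated to cancer. The Background section makes this plausible: the existing evidence of effectiveness comes from benign gynecological surgery, and colectomy is the new population. The contrast would then show a weaker effect in malignant disease even if malignancy plays no part. Extension to malignant indications is one of the article's stated conclusions, so this subgroup result is likely to be noticed and interpreted.

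**Working it through.** **Step 1: which combinations are eligible.**

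| | Colectomy | Hysterectomy |
|---|---|---|
| Benign | eligible | eligible |
| Malignant | eligible | excluded |

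This follows from the Eligibility Criteria alone and needs no assumption.

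**Step 2: whether other parts of the plan remove the overlap.** Procedure is a covariate in the adjusted primary analysis. A main effect of procedure lets the baseline hazard differ between procedures, but does not let the treatment effect differ. It therefore cannot separate treatment-by-indication from treatment-by-procedure. Stratified randomization balances the arms; the mixing here is between subgroups, so stratification does not address it.

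**Step 3: size, by illustration.** The plan gives no subgroup figure to reproduce, and it gives neither the case mix nor procedure-specific effects. Assumed inputs:

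- h, the share of hysterectomies: 0.40 to 0.60
- m, the share of colectomies that are malignant: 0.60 to 0.90
- true hazard ratio 1.6 in hysterectomy and 1.2 in colectomy, the same for either indication
- events proportional to patients, so that patient shares serve as weights

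Formulas:

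- malignant share of all patients M = (1 − h)m
- hysterectomy share of the benign group s = h / (1 − M)
- correlation of indication with procedure (phi) = √(mh / (1 − M))
- apparent benign hazard ratio = exp[s ln 1.6 + (1 − s) ln 1.2]
- apparent malignant hazard ratio = 1.2, its true value
- apparent benign/malignant ratio = (1.6/1.2)^s

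| h | m | M | s | phi | Benign HR | Ratio (true 1.00) |
|---|---|---|---|---|---|---|
| 0.40 | 0.60 | 0.36 | 0.625 | 0.61 | 1.44 | 1.20 |
| 0.40 | 0.90 | 0.54 | 0.870 | 0.88 | 1.54 | 1.28 |
| 0.60 | 0.60 | 0.24 | 0.789 | 0.69 | 1.51 | 1.25 |
| 0.60 | 0.90 | 0.36 | 0.938 | 0.92 | 1.57 | 1.31 |

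First row: s = 0.40/0.64 = 0.625, and (1.333)^0.625 = 1.20. Last row: s = 0.60/0.64 = 0.938, and (1.333)^0.938 = 1.31.

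**Step 4: precision of each contrast.** Take the planned 354 patients with 10% dropout and 2.5% not resuming activities: 354 × 0.9 × 0.975 ≈ 311 events. With var(log HR) = 4/events in each group:

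- *All patients, benign v malignant.* SE of the log ratio = √(4/E_mal + 4/E_ben). Over the four rows this is 0.23 to 0.27, so a 95% interval extends by a factor of about 1.56 to 1.68 either way. A spurious ratio of 1.20 to 1.31 would reach two-sided 5% significance about 12 to 21% of the time.
- *Colectomies only, benign v malignant.* At h = 0.40, m = 0.60 there are about 112 malignant and 75 benign colectomy events: SE = √(4/112 + 4/75) = 0.30, and the ratio detectable with 80% power is exp(2.80 × 0.30) ≈ 2.3. At h = 0.60, m = 0.90 the events are about 112 and 12: SE = 0.60, detectable ratio about 5.3. With colectomies at 30 to 70% of patients instead, the detectable ratio runs from about 2.2 to 6.9.

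**The case against.** **The two factors can be separated.** A reader might infer from the empty cell that the trial can never tell indication from procedure. The documents do not support that. Benign colectomies are eligible, so the overlap is partial: indication can be examined within colectomy, and procedure within benign patients. This objection stands, and the fix relies on it.

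**The effect in malignant patients is not biased.** A reader might also infer that the subgroup result would be wrong about whether the tool works in malignant disease. It would not. The randomized comparison within malignant patients is valid, and in the illustration it returns 1.2, the assumed true value. It is limited to malignant colectomy, which is the only malignant population admitted. What is confounded is the explanation of a difference between the benign and malignant results. This stands in full.

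**The pooled contrast is a reading of one sentence.** The article does not say that benign and malignant hazard ratios will be formally compared, or that a difference will be ascribed to malignancy, and an analysis plan that is not shown may specify the model. This stands in part. The point, however, is not that detail is missing: the sentence names two parallel factors without restriction, and the article's own eligibility rule makes one of them largely or partly a copy of the other.

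**The numbers are assumed, and the distortion is small beside the noise.** Both are true. The shares and hazard ratios are not in the documents, and the spurious ratio lies within the sampling error of the contrast. That the contrast mixes the two factors does not depend on the numbers.

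**Conclusion.** The point holds in a limited form. By the trial's own eligibility rule, the malignant subgroup is all colectomy and every hysterectomy is benign. An indication contrast over all patients therefore partly repeats the procedure and sex contrast, and a benign-malignant difference in effect cannot be attributed to malignancy.

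Under the assumed case mix and hazard ratios, the spurious benign/malignant ratio is 1.20 to 1.31. If the effect did not differ by procedure or sex, there would be no distortion. The direction depends on which procedure benefits more, and the size depends on shares that the documents do not give.

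The primary estimate, the sample size and the hazard ratio within malignant patients are not affected. This is worth correcting because the extension to malignant indications is a prominent aim, but it remains a matter of subgroup interpretation.

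**What to change.** Amend the subgroup wording as follows:

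- Base any treatment-by-indication contrast on colectomies only (malignant v benign colectomy). Alternatively, fit treatment-by-indication and treatment-by-procedure interactions in one model.
- Report the interaction with its confidence interval and label it exploratory.
- Hazard ratios by indication may still be shown descriptively, with a note that the malignant group is all colectomy and that the benign group includes every hysterectomy.
- State that the trial supports no conclusion about malignant hysterectomy.

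This changes wording only: no added patients, data or procedures. The price is precision. Only colectomies inform the contrast, and the number of benign ones is not given. Under the assumptions above, only a ratio of hazard ratios of about 2.2 or more, and possibly as high as 6.9, would be detectable with 80% power. The result should be presented as an estimate with a wide interval, and a non-significant interaction should not be read as evidence of equal effect.

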## Discussion

### Principal Findings

The purpose of this study was to describe the systematic process of the further development of the “ikherstel” intervention following the 6 steps of the IM protocol [20,21]. This eHealth intervention was adjusted to target different behavioral determinants relevant for the overarching program goal to achieve earlier full recovery for general surgical and gynecological patients. From the beginning, patients and health care professionals were involved in the developmental process and patients’ needs were taken into account by offering a user-friendly eHealth and mHealth intervention for our target group [67]. By involving hospitals in an early stage of the development process, the expectation is that a supportive basis for the intervention was created and that the implementation followed by evaluation will go as planned [68].

### Comparison With Other Studies

The IM protocol has proven to be suitable to systematically and scientifically develop an eHealth intervention for various health issues [69,70]. In addition, a few studies have also used the IM protocol to further develop, adapt, or adjust an existing intervention [71,72]. In these studies, the IM protocol was considered suitable and enabled researchers to reconsider points of view and to integrate new information into existing tools. These studies used the IM protocol in the same manner as we did in this study. They decided to further build on the methodological choices made in the previously developed intervention by adjusting and improving the existing intervention for a new study population [71,72]. Methodological choices made in steps 2 and 3 of the IM process of developing the original “ikherstel” intervention, as described in the IM article of Vonk Noordegraaf et al, are considered effective and, therefore, used again in this IM procedure [19].

Comparison with other studies focusing on the development of eHealth recovery interventions is limited due to a low number of studies [18,23]. When comparing this developed intervention to the eHealth interventions included in the systematic review conducted by our planning group in step 1, it can be concluded that our intervention consists of multiple components on a diversity of functions that makes this a comprehensive intervention. In addition, most RCTs regarding enhancing the postoperative course are performed in cardiac surgery, whereas there is a lack of RCTs evaluating postoperative recovery after general surgical and gynecological procedures [73-80]. The studies of Vonk et al and Bouwsma et al are most comparable [18,23]. However, our study will be the only RCT that will be performed in patients undergoing major abdominal surgery focusing on RNA, which also includes procedures performed due to a malignant indication [81]. By determining the time until RNA as primary outcome, all patients aged between 18 and 75 years can participate in this study allowing more people to be reached.

The intervention was further developed and improved with respect to the previous “ikherstel” intervention. The shortcomings identified in the needs assessment are reflected, and new tools have been introduced. On the basis of the input from the FGDs, the accessibility has been improved by developing a mobile app and by the possibility of an eConsult. This facilitates direct access and communication with health care professionals and increases the reach of the “ikherstel” intervention [82]. By using the activity tracker, patients can monitor themselves, resulting in more involvement in their recovery process and motivating them to mobilize quicker and more intensively. Given the “ikherstel” intervention is based on the concept of computer-driven tailoring, the information regarding recovery is more personally relevant, which will increase the likelihood of behavior change and maintenance [83,84].

### Strengths and Limitations

One of the strengths of our study is that by involving patients and different health care professionals in the development process of the intervention, experiences from multiple fields of expertise were included. We are convinced that this is necessary because this recovery-focused eHealth intervention is designed to include a multidisciplinary approach. Another strength is that all information gathered in the development (IM) process of the original intervention was based on findings of qualitative and quantitative studies and is used and extended with additional information obtained during this IM process. By adjusting and improving the “ikherstel” intervention, a more complete eHealth intervention for the broadened target population was created.

A limitation is that nurses were not involved in this process of development of the intervention, whereas they are linked to a part of the intervention itself. However, we did have meetings with nurses in step 5 of the IM protocol, which attributes to the acceptability.

### Clinical Relevance

Involving different program users and using a theory- and evidence-based systematic approach in the development of the intervention as noted in the IM procedure results in the best opportunity on effectiveness and implementation. If the further developed “ikherstel” intervention is proven effective, the content can be extended to other surgical procedures. In addition, if it proves to be cost-effective for a broad surgical group of patients, an implementation plan for future nationwide implementation has to be generated. It will also provide insight into the question of whether a systematically further developed version of an effective intervention is still effective for a different target group.

### Conclusions

This study showed that with the use of IM, we were able to optimize and further develop the original “ikherstel” intervention. The intervention is extended to patients undergoing general surgical procedures and for malignant indications. New intervention tools such as a mobile app, an activity tracker, and an eConsult were developed. Consequently, with these tools, there is an increase in accessibility coupled with provision of monitoring and interactive feedback. The further developed “ikherstel” intervention will be evaluated in a multicenter single-blinded RCT.

## Appendix

Multimedia Appendix 1 Performance objectives to empower patients to return to normal activities including work. Asterisk indicates that the performance objective is based on the intervention mapping study of Vonk Noordegraaf et al (2014).

Multimedia Appendix 2 Example of performance objective of patients.

Multimedia Appendix 3 Determinants, methods, preconditions and strategies tools.

Multimedia Appendix 4 The layout of the mobile app (directly translated from Dutch).

Multimedia Appendix 5 Primary and secondary outcomes per measurement moment.

## Abbreviations

eConsult: electronic consultation
eHealth: electronic health
ERAS: enhanced recovery after surgery programs
FGD: focus group discussion
ICT: information and communication technology
IM: Intervention Mapping
mHealth: mobile health
PRECEDE: predisposing, reinforcing, and enabling constructs in educational diagnosis and evaluation
PROCEED: policy, regulatory, and organizational constructs in educational and environmental development
RCT: randomized controlled trial
RNA: resumption of normal activities
RTW: return to work
